### ***Exemptions from SAE Report submission***

For this trial, the following events are exempt from requiring submission on an SAE Report, but must be recorded in the relevant section(s) of the trial eCRFs:

- events that occur more than 110 days post last trial treatment administration unless:
  - considered to be a late effect of the trial treatment
  - it is a pregnancy related event (see section 13.6)
- disease progression (including disease progression and disease related deaths) unless:
  - considered related to the IMP.

Please note that hospitalisation for elective treatment, palliative care or logistic/social reasons does not qualify as an SAE.

**Completed SAE Reports must be faxed or emailed to UCL CTC within  
24 hours of becoming aware of the event**

**[contact]**  
**Email: [[contact]](mailto:[contact])**

### ***SAE Follow-Up Reports***

All SAEs must be followed-up until resolution and until there are no further queries. Sites must ensure any new and relevant information is provided promptly. If the event term changes or a new event is added, the causality must be re-assessed by an Investigator. If the event is not being reported **within 24 hours** to UCL CTC, the circumstances that led to this must be detailed in the SAE/SAR Report to avoid unnecessary queries.

Adverse Event Reporting Flowchart on the following page.

## PEACOCC

[figure not shown]

\* This applies if AE, SAE and AESI reporting period differs

### SAE Processing at UCL CTC

On receipt of the SAE Report, UCL CTC will check for legibility, completeness, accuracy and consistency. UCL CTC will evaluate expectedness, to determine whether or not the case qualifies for expedited reporting, using the RSI (the list of expected adverse events in the approved IB for pembrolizumab).

The CI, or their delegate (e.g. a clinical member of the TMG), will be contacted to review the SAE and to perform an evaluation of causality on behalf of UCL CTC. If UCL CTC has considered expectedness difficult to determine, the CI, or their delegate, will be consulted for their opinion at this time.

UCL CTC will submit all SAE Reports concerning patients who have received pembrolizumab to MSD according to the timelines outlined in the agreement between UCL and MSD.

### 13.3. SUSARs

If the event is evaluated as a SUSAR, i.e. an unexpected event that is related (reasonable possibility) to the investigational drug, UCL CTC will submit a report to the MHRA and the REC within 7 calendar days for initial reports of fatal/life threatening events (with a follow-up report within a further 8 calendar days) and 15 calendar days for all other events. Wherever possible, evaluations of causal relationship by both the site and the Sponsor's clinical reviewer will be reported.

UCL CTC will submit all SUSAR reports relating to pembrolizumab to MSD according to the timelines outlined in the agreement between UCL and MSD.

#### *Informing Sites of SUSARs*

UCL CTC will inform all PIs of any SUSARs that occur on the trial. PIs will receive a quarterly line listing which must be processed according to local requirements.

UCL CTC will forward any reports received from MSD regarding SUSARs that have occurred on other trials using pembrolizumab to all PIs. These must be processed according to local requirements and filed with the applicable IB.

### 13.4. Adverse events of special interest

The following adverse events of special interest for pembrolizumab must be reported on an SAE report within **24 hours of becoming aware of the event** between the signing of informed consent and 110 days after the date of last IMP administration:

- An overdose of Pembrolizumab, as defined in Section 9.6
- Abnormal liver function tests meeting ALL the following criteria:
  - an elevated AST or ALT lab value that is greater than or equal to 3X the upper limit of normal **AND**
  - an elevated total bilirubin lab value that is greater than or equal to 2X the upper limit of normal **AND**,
  - an alkaline phosphatase lab value that is less than 2 x the upper limit of normal, as determined by way of protocol-specified laboratory testing or unscheduled laboratory testing.\*

## PEACOCC

---

\*Note: These criteria are based upon available regulatory guidance documents. The purpose of the criteria is to specify a threshold of abnormal hepatic tests that may require an additional evaluation for an underlying aetiology.

**All AEs of special interest must be reported by faxing a completed SAE report to UCL CTC within 24 hours of becoming aware of the event**

**[contact]**

**Email: [[contact]](mailto:[contact])**

### 13.5. Safety Monitoring

UCL CTC will provide safety information to the Trial Management Group (TMG) and the Independent Data Monitoring Committee (IDMC) on a periodic basis for review.

Trial safety data will be monitored to identify:

- new adverse reactions to the trial treatment regimen or individual trial treatments
- a higher incidence in rare adverse events than is stated in the IB for a trial treatment
- trial related events that are not considered related to the trial treatment regimen

If UCL CTC identifies or suspects any issues concerning patient safety at any point during the trial, the CI or TMG will be consulted for their opinion, and if necessary the issue will be referred to the IDMC.

### 13.6. Pregnancy

#### ***Reporting Period***

If a female patient becomes pregnant between the start of trial treatment and 120 days after last trial treatment administration (or 30 days following cessation of treatment if the patient initiates a new anticancer therapy, whichever is earlier) the site must submit a trial specific Pregnancy Report to UCL CTC by fax or email **within 24 hours** of learning of its occurrence.

The site must request consent from the pregnant trial patient to report information regarding a pregnancy using:

- The trial-specific Pregnancy Monitoring Information Sheet and Informed Consent Form for trial patients

If consent is not given, the notification that a pregnancy has occurred will be retained by UCL CTC, however no further action will be taken on the information detailed in the report.

**All pregnancies must be reported by faxing or emailing a completed Pregnancy Report to UCL CTC within 24 hours of becoming aware of the pregnancy**

**[contact]**

**Email: [[contact]](mailto:[contact])**

### ***Pregnancy Follow-Up Reports***

Pregnant patients who consent to pregnancy follow-up, must have their pregnancies followed -up at least monthly for up to 6 weeks after the end of the pregnancy (or later if there are ongoing issues) to collect information on any ante- and post-natal problems for both mother and child. If significant new information is received, follow-up Pregnancy Reports must be submitted to UCL CTC by fax or email within 24 hours of learning of the information. In the case of an adverse outcome to the pregnancy (e.g. miscarriage), reports must include an evaluation of the possible relationship between the trial treatment and the pregnancy outcome. SAEs during pregnancy

Any SAE occurring in a pregnant patient must be reported using the trial specific SAE Report, according to SAE reporting procedures. Refer to section 13.2.2 (Reporting of Serious Adverse Events (SAEs)) for details.

### ***Pregnancy Report processing at UCL CTC***

UCL CTC will submit a report to the MHRA and the REC if the pregnancy outcome meets the definition of a SUSAR. Refer to section 13.3 (SUSARs) for details.

UCL CTC will submit all Pregnancy Reports concerning exposure to pembrolizumab to MSD according to the timelines outlined in the agreement between UCL and MSD.

## **13.7. Development Safety Update Reports (DSURs)**

Safety data obtained from the trial will be included in DSURs that UCL CTC will submit to the MHRA and the REC.

UCL CTC will provide MSD with DSURs that include information regarding pembrolizumab.

## **14. INCIDENT REPORTING AND SERIOUS BREACHES**

### **14.1. Incident Reporting**

Organisations must notify UCL CTC of all deviations from the protocol or GCP immediately. An incident report may be requested and will be provided, but an equivalent document (e.g. Trust Incident form) is acceptable where already completed. Where an equivalent document is being submitted to UCL CTC, the patient's trial number must be clearly indicated on all material and any patient identifiers redacted prior to sending, to maintain confidentiality.

If site staff are unsure whether a certain occurrence constitutes a deviation from the protocol or GCP, the UCL CTC trial team can be contacted immediately to discuss.

UCL CTC will use an organisation's history of non-compliance to make decisions on future collaborations.

UCL CTC will assess all incidents to see if they meet the definition of a serious breach.

### **14.2. Serious Breaches**

A "serious breach" is defined as a breach of the protocol or of the conditions or principles of Good Clinical Practice which is likely to affect to a significant degree the safety or physical or mental integrity of the trials, or the scientific value of the research.

Systematic or persistent non-compliance by a site with GCP and/or the protocol, including failure to report SAEs occurring on trial within the specified timeframe, may be deemed a serious breach.

In cases where a serious breach has been identified, UCL CTC will inform the MHRA and REC within 7 calendar days of becoming aware of the breach.

Sites must have written procedures for notifying the sponsor of serious breaches (MHRA Guidance on the Notification of Serious Breaches).

## 15. TRIAL MONITORING AND OVERSIGHT

Participating sites and PIs must agree to allow trial-related on-site monitoring, Sponsor audits and regulatory inspections by providing direct access to source data/documents as required. Where permitted by site policy, remote access to source data/documents may also be provided by participating sites for remote monitoring by UCL CTC or its representatives.

Patients are informed of this in the patient information sheet and are asked to consent to their medical notes being reviewed by appropriate individuals on the consent form. UCL CTC or its representatives will conduct all monitoring in compliance with the participant consent, site policy and data protection requirements.

UCL CTC will determine the appropriate level and nature of monitoring required based on the objective, purpose, phase, design, size, complexity, endpoints and risks associated with the trial. Risk will be assessed on an ongoing basis and adjustments made accordingly.

Details of monitoring activities will be included in the trial monitoring plan and conveyed to sites during initiation. The Monitoring Plan will be kept under review during the trial and updated information provided to sites as necessary.

### 15.1. On-Site and Remote Monitoring

#### On-site Monitoring

Sites will be sent an email in advance of any on-site monitoring visits, confirming when a visit is scheduled to take place. The email will include a list of the documents to be reviewed, interviews that will be conducted, planned inspections of the facilities and who will be performing the visit.

#### Remote Monitoring

UCL CTC defines remote monitoring as activities conducted at a location remote from the research site which replicate some on-site activities e.g. source data review. Remote monitoring may be conducted in response to exceptional circumstances preventing access to participating sites (e.g. global pandemic) or conducted routinely. Details of remote monitoring will be agreed with participating sites, conducted in accordance with site policy and documented in the monitoring plan.

Sites will be sent an email in advance, confirming when remote monitoring is scheduled to take place and how the source documents will be remotely accessed. The email will include a list of the documents to be reviewed, interviews that will be conducted via telephone/videoconference and who will be performing the remote monitoring.

Remote monitoring will be conducted by UCL CTC or its representatives via a device with adequate security. Patient confidentiality will be maintained at all times, and monitoring activities will be conducted in an appropriate environment where no unauthorised viewing or overhearing of conversations is possible by third parties. Refer to section 12 Data Management and Data Handling Guidelines for details of how source documentation should be submitted to UCL CTC.

## PEACOCC

---

### **Monitoring Follow Up**

Following on-site remote monitoring, the Trial Monitor/Trial Coordinator will provide a follow up email to the site, which will summarise the documents reviewed and a statement of findings, incidents, deficiencies, conclusions, actions taken and/or actions required. The PI at each site will be responsible for ensuring that monitoring findings are addressed in a timely manner, and by the deadline specified.

### **15.2. Centralised Monitoring**

UCL CTC performs centralised monitoring, which requires the submission of the following documents by sites to UCL CTC for review: screening logs, staff delegation logs and accountability logs. Expectations for document submission will be explained during site initiation and UCL CTC or its representatives will send emails to sites requesting the documents when required.

Sites will be requested to conduct quality control checks of documentation held within the Investigator Site File and Pharmacy Site File at the frequency determined for the trial. Checklists detailing the current version/date of version controlled documents will be provided by UCL CTC for this purpose.

### **15.3. Triggered' On-Site/Remote Monitoring**

Additional on-site or remote monitoring visits may be scheduled following UCL CTC review and/or where there is evidence or suspicion of non-compliance at a site with important aspect(s) of the trial protocol/GCP requirements.

#### **On-site Monitoring**

Sites will be sent an email in advance outlining the reason(s) for the visit and confirming when it will take place. The email will include a list of the documents that are to be reviewed, interviews that will be conducted, planned inspections of the facilities and who will be performing the visit.

#### **Remote Monitoring**

Sites will be sent an email in advance, confirming when remote monitoring is scheduled to take place and how the source documents will be remotely accessed. The email will include a list of the documents to be reviewed, interviews that will be conducted via telephone/videoconference and who will be performing remote monitoring.

## **15.4. Escalation of monitoring issues**

Where monitoring indicates that a patient may have been placed at risk (e.g. evidence of an overdose having been administered, indication that treatment discontinuation rules were not observed following an adverse reaction, etc), the matter will be raised urgently with site staff and escalated as appropriate.

UCL CTC will assess whether it is appropriate for the site to continue participation in the trial and whether the incident(s) constitute a serious breach. Refer to section for details.

## **15.5. Oversight Committees**

### **15.5.1. Trial Management Group (TMG)**

The TMG will include the Chief Investigator, clinicians and experts from relevant specialties, PEACOC trial staff from UCL CTC and a patient representative (see page 2). The TMG will be responsible for overseeing the trial. The group will meet regularly and will send updates to PIs (via newsletters or at Investigator meetings) and to the NCRI Gynaecological Clinical Studies Group.

The TMG will review substantial amendments to the protocol prior to submission to the REC and MHRA. All PIs will be kept informed of substantial amendments through their nominated responsible individual and are responsible for their prompt implementation.

All TMG members will be required to sign a UCL CTC TMG Charter.

### **15.5.2. Trial Steering Committee (TSC)**

The role of the TSC is to provide overall supervision of the trial. The TSC will review the recommendations of the Independent Data Monitoring Committee and, on consideration of this information, recommend any appropriate amendments/actions for the trial as necessary. The TSC acts on behalf of the funder and the Sponsor.

All TSC members will be required to sign a UCL CTC TSC Charter.

### **15.5.3. Independent Data Monitoring Committee (IDMC)**

The role of the IDMC is to provide independent advice on data and safety aspects of the trial. Meetings of the Committee will be held at least annually to review interim analyses or as necessary to address any issues. The IDMC is advisory to the TSC and can recommend premature closure of the trial to the TSC.

All IDMC members will be required to sign a UCL CTC Charter.

### **15.5.4. Role of UCL CTC**

UCL CTC, on behalf of the Sponsor (UCL) will be responsible for the day to day coordination and management of the trial and the UCL CTC Director will act as custodian of the data generated in the trial (on behalf of UCL). UCL CTC is responsible for all duties

## PEAC OCC

---

relating to pharmacovigilance which are conducted in accordance with section 13 (Pharmacovigilance ).

## 16. WITHDRAWAL OF PATIENTS

In consenting to the trial, patients are consenting to trial treatment, assessments, collection of biological samples, follow-up and data collection.

### 16.1. Patient Withdrawal/Discontinuation Criteria

A patient may be withdrawn from the trial or trial treatment whenever such treatment is no longer in the patient's best interests. The reasons for withdrawal from treatment must be recorded in the patient's notes and on the relevant Case Report Form(s).

Reasons for discontinuing treatment may include:

- Patient's decision to discontinue treatment.
- Confirmed radiographic disease progression  
*Note: For unconfirmed radiographic disease progression, please see Section 16.1.2.*
- Unacceptable adverse events as described in Section 5.
- Intercurrent illness that prevents further administration of treatment.
- Investigator's decision to withdraw the patient from treatment.
- The patient has a confirmed positive urine or serum pregnancy test or fails to use adequate contraceptive methods.
- Non-compliance with trial treatment or procedure requirements.
- The patient is lost to follow-up.
- Completed 24 months of uninterrupted treatment with pembrolizumab or 35 administrations of study medication, whichever is later.  
*Note: 24 months of study medication is calculated from the date of first dose. Patients who stop pembrolizumab after 24 months may be eligible for up to one year of additional study treatment if they progress after stopping study treatment provided they meet the requirements detailed in Section 9.3.2.*

After the end of treatment, each patient will be followed up for safety monitoring as per Section 13.2.2. The end of treatment and follow-up visit procedures are listed in Appendix 1 (Trial Schedule of Procedures/Assessments) and Section 10.4.2 (Visit Requirements).

If a patient expresses their wish to withdraw from the trial either during treatment or while in follow-up, sites should explain the importance of remaining on trial follow-up, or failing this of allowing routine follow-up data to be used for trial purposes and for allowing existing collected data to be used. If the patient gives a reason for their withdrawal, this should be recorded on the relevant eCRF(Change of Status).

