## 9.11. Clinical Management after Treatment Discontinuation

If a patient discontinues trial treatment early, they will remain on trial for follow up purposes unless they explicitly withdraw consent. Also refer to sections 10 (Assessments) and 16 (Withdrawal of Patients) for further details regarding treatment discontinuation, patient withdrawal from trial treatment and withdrawal of consent to data collection.

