#### 10.4.2.3 Post-Treatment Visits

Appendix 1 'Schedule of Procedures/Assessments' shows all procedures to be conducted during the follow-up period.

All patients are required to attend the end of treatment visit, all follow-up visits and to be contacted by the research team for survival status in accordance with the Schedule of Procedures/Assessments in Appendix 1. However, if a patient discontinues from treatment, has progressed and moves onto alternative anticancer treatment, the follow-up visits will no longer be required; however, survival follow-up assessments and collection of subsequent anticancer therapy information would be required as indicated in the Schedule of Assessments/Procedures, Appendix 1 unless the patient withdraws consent for further survival follow-up. Survival follow-up will continue until the end of study.

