### 10.6.1. Survival Follow-up

Once a patient experiences confirmed disease progression or starts a new anti-cancer therapy, the patient moves into the survival follow-up phase and should be contacted by telephone every 12 weeks to assess for survival status and any AEs that require reporting as per section 13.2, until death, withdrawal of consent, or the end of the study, whichever occurs first.

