### **18.2.2.3. Overall survival**

Overall survival is defined as the time from start of treatment to death from any cause. All deaths will be included, whether they occur on study or following treatment discontinuation. For patients who have not died, overall survival will be censored at the date of last contact.

Kaplan-Meier survival methods will be used.

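### Section 16.1 permits withdrawal from the trial on a ground that concerns treatment only, contradicting the follow-up rules in 9.11, 10.4.2.3 and 10.6.1 and opening a possible route to informative censoring of OS and PFS

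*Protocol*

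**What the plan says.** Section 16.1 begins: "A patient may be withdrawn from the trial or trial treatment whenever such treatment is no longer in" the patient's best interests. The sentence covers two different exits, leaving the trial and stopping the drug, and gives both the same ground.

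Other sections describe what happens once treatment stops:

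- Section 9.11: "If a patient discontinues trial treatment early, they will remain on trial for follow up purposes unless they explicitly withdraw consent".
- Section 10.4.2.3, on post-treatment visits: "Survival follow-up will continue until the end of study". The exception it makes is "unless the patient withdraws consent for further survival follow-up".
- Section 10.6.1: telephone survival follow-up runs "until death, withdrawal of consent, or the end of the study, whichever occurs first".
- Section 10.6: disease follow-up before progression ends at progression, death, withdrawal of consent or loss to follow-up. A later paragraph adds end of study and start of re-treatment.

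On analysis, section 18.2.2.3 states: "For patients who have not died, overall survival will be censored at the date of last contact". Section 18.2.2.1 has the matching rule for PFS. Both sections also intend to count every death, including deaths after treatment has been discontinued.

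**The concern.** None of the follow-up sections recognises withdrawal from the trial because treatment no longer serves the patient. A site cannot act on that part of 16.1 and also comply with 9.11. The plan to count deaths after treatment discontinuation likewise depends on follow-up continuing.

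The ground in 16.1 will often be met by a patient who is getting worse. If she were taken out of the trial at that point, her survival time would be censored at last contact, shortly before the event. Kaplan-Meier estimation assumes that censored patients have the same outlook as those still at risk, and here theirs would be worse. The estimates would move upward, and a single-arm trial has no control group in which the same distortion would occur. Duration of response (18.2.2.5) and time to second progression (18.2.2.2) are also censored at last contact and share the exposure.

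Such cases could also be hard to find afterwards. Section 16.1 asks sites to record reasons for withdrawal from treatment, and any reason given by a patient who herself wishes to leave. It asks for no reason when someone else removes her from the trial.

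**Working it through.** **1. The plan's own figure.** Section 18.1 gives 48 patients and a cut-off of 12 progression-free at 12 weeks, for 33% against 15%, with 90% power and one-sided 5% significance. Exact binomial, X the number of successes among 48:

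- P(X ≥ 12 | p = 0.15) = 0.0478
- P(X ≥ 12 | p = 0.33) = 0.911

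Searching n upward from 20, 48 with cut-off 12 is the first design that meets both targets. The design reproduces, and nothing below changes it.

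**2. The passages side by side.**

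| Section | What can end follow-up |
|---|---|
| 16.1, opening sentence | Withdrawal from the trial because treatment no longer serves the patient |
| 9.11 | Explicit withdrawal of consent |
| 10.4.2.3 (survival) | End of study, or withdrawal of consent for it |
| 10.6.1 (survival) | Death, withdrawal of consent, end of study |
| 10.6 (disease status) | Progression, death, withdrawal of consent, loss to follow-up, end of study, re-treatment |

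The first row has no counterpart in the others.

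**3. Direction and rough size for the Kaplan-Meier endpoints.** The protocol gives no withdrawal fraction, no expected median OS and no interval from withdrawal to event. All three are assumptions here.

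Let event times be exponential with hazard λ, and let a fraction f, unrelated to the length of the event time, be censored just before the event. Only a share 1-f of events is then seen at each time, so the curve estimates exp(-(1-f)λt). Its median is

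ln 2 / ((1-f)λ) = true median / (1-f).

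For an assumed median OS of 10 months: 10/0.95 = 10.5, 10/0.90 = 11.1 and 10/0.80 = 12.5 months.

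A simulation with 400,000 exponential times lets the censoring fall a fixed interval before the event: 1 month for OS and 3 weeks for PFS. The PFS hazard is set so that 33% are progression-free at 12 weeks, λ = -ln(0.33)/12 per week, which gives a true median of 7.5 weeks.

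| Fraction withdrawn f | Patients of 48 | Median OS, months (true 10) | 12-month OS (true 43.5%) | Median PFS, weeks (true 7.5) |
|---|---|---|---|---|
| 5% | 2.4 | 10.5 | 45.3% | 7.8 |
| 10% | 4.8 | 11.0 | 47.0% | 8.1 |
| 20% | 9.6 | 12.3 | 50.9% | 8.9 |

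The results lie at or a little below median/(1-f). The gap is wider for PFS (7.5/0.80 = 9.4 against 8.9), because 3 weeks is a large part of a 7.5-week median.

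**4. The primary endpoint.** Section 18.2.1 counts a patient as progression-free only if she has a tumour assessment at or beyond 12 weeks. A patient withdrawn before then counts as a failure, so this route cannot raise the primary proportion.

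**The case against.** The strongest reply is that this is one loose phrase in a section otherwise about treatment. The next sentence of 16.1 concerns reasons for withdrawal from treatment, and the list that follows is headed as reasons for discontinuing treatment. Its entry for the investigator's decision is limited to treatment. The section then points to the follow-up procedures, and asks sites to explain the value of staying in follow-up to any patient who wishes to leave. A site would have to overlook all this, as well as 9.11, 10.4.2.3 and 10.6.1, to stop following a patient. That reply stands as to likelihood: the words look like a drafting remnant. It does not remove the permission.

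Three stronger readings are tempting, and the documents do not support them.

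- *The investigator is given power to remove patients from the trial.* The sentence is passive and names no one. A decision made for the patient is the natural reading, because her own wish is handled later in 16.1, but it remains an inference.
- *Serious events in the 110 days after the last dose could be lost.* Section 16.1 itself keeps each patient in safety follow-up under 13.2.2 after treatment ends. Section 13.2.2 requires SAE reporting to 110 days for every registered patient who received treatment, with no exception for withdrawal.
- *OS and PFS are inflated.* The text makes this possible and no more. A patient already recorded as progressed has her PFS event and cannot be affected, and one withdrawn for toxicity with controlled disease need not bias the estimate upward.

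It is also true that OS and PFS are secondary, descriptive endpoints without a test or threshold, so the decision rule does not depend on them.

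**Conclusion.** The contradiction between the opening of 16.1 and sections 9.11, 10.4.2.3 and 10.6.1 is real and should be removed. Its statistical consequence is conditional. If sites used the permission for deteriorating patients, and no later survival status were obtained, OS would be biased upward, as would PFS for those not yet progressed. The size cannot be stated from the protocol. The factor of roughly 1/(1-f) rests on exponential times, withdrawal shortly before the event and an assumed f. The fractions of 5% to 20% illustrate the effect and do not predict it.

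The primary 12-week result is outside the reach of this bias, since any distortion there could only lower it. The sample size, the cut-off of 12 and the 110-day SAE reporting duty are untouched.

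**What to change.** In the opening sentence of 16.1, delete the three words *the trial or*, so that it covers withdrawal from trial treatment only. Add a cross-reference to 9.11, 10.4.2.3, 10.6, 10.6.1 and 16.3 for when follow-up ends:

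- imaging, at progression or the start of new anti-cancer therapy, besides the general ends to disease follow-up in 10.6;
- survival follow-up, at death, withdrawal of consent, loss to follow-up or end of study.

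The cross-reference is safer than a new blanket rule. Stating that follow-up ends only on withdrawal of consent would omit loss to follow-up (10.6, 16.3). Stating that everyone taken off treatment continues imaging would conflict with 10.4.2.3, 10.5 and 10.6.1 for patients who have progressed or started other therapy.

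The cost is a wording change in one sentence plus the cross-reference. It adds no visits, alters no rule for stopping treatment and leaves every design figure as it is.
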